### Sample size

The sample size calculation is based on a power calculation for the primary outcome i.e. the Skills and Technique acquisition scale of the heiQ at T1. Previous studies have shown effect sizes (Cohen’s *d*) of similar interventions on the Skills and Technique Acquisition scale of 0.17, 0.50, 0.25, 0.50, 0.31 and 0.59 [49–54]. Based on these previous results, we estimate the effect size of the intervention to be 0.38, which is the average effect size observed in the previous studies. Using an ANCOVA model applied at the patient level, with an adjustment for baseline Skills and Technique Acquisition and treatment group (pre- or post-intervention), 82 patients per group are needed to obtain a power of 80% to detect a significant effect of the intervention, at a two-sided significance level of .05. To account for the effects of adjustment for covariates, dropout and missing data, and contamination, we aim to include 100 patients per group, 200 in total. Note that the ANCOVA model assumed in the power analysis differ slightly from the linear mixed model described for the primary analysis below.

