### Data analysis

Data will be coded with a unique code per patient. The key of these codes will be safeguarded by the coordinating and the principal investigator with a password. No other persons will have access to the key. All data will be kept for 15 years, according to the Dutch Personal Data Protection law. Data will be stored using the data capture applications Gemstracker and Limesurvey. These systems are managed by the Department of Information Management of Erasmus MC and are secured with an individual password for the coordinating and principal investigator.

To assess if randomization has resulted in comparable groups, we will compare patients in the control and in the experimental period at baseline (T0) on characteristics as well as primary and secondary outcomes. Descriptive statistics will be presented as frequencies (%) for categorical variables. Continuous variables will be described as median and interquartile range for non-normally distributed variables and as mean and standard deviation for normally distributed data.

The primary analysis of the study is an initial univariate exploration of the effect of the intervention. Continuous outcomes at T1 between the patients in the control and experimental period will be compared and tested using the Mann-Whitney *U* test for non-normally distributed data and the independent-samples *t* test for normally distributed data. For the BAASIS, a 2 × 2 chi-squared test will be conducted (adherent yes/no × control/experimental group). In univariate analyses, the relationship between patient characteristics (such as age and gender) and medical characteristics (such as organ type and centre) and the outcomes will be assessed.

For the multivariate analyses, linear mixed models analysis will be conducted to account for repeated measures per patient, covariates organ and transplant centre and other significant covariates. All models will be estimated using intention-to-treat analysis incorporating all eligible patients from whom data was obtained. There are three measurement time points (T0, T1 and T2) to be included in these analyses. For missing data in predictor variables, we will use multiple imputation. A *p* value < 0.05 is considered statistically significant.

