We will assess the differences on the primary and secondary outcomes between patients in the control period and versus the experimental period at both T1 and T2 on the outcomes (between-groups comparison). We will also assess the differences on the outcomes between T0–T1 and T0–T2 within the control period and within the experimental period (within-groups comparison). The secondary outcome measure *medication adherence*, which is a dichotomous variable, will be analysed with a generalized estimating equations logistic regression. If the effect of the intervention is found to differ according to organ type then separate explorative multivariate analyses will be conducted to assess the effect per organ.

Among NPs, in an initial univariate analysis, we will compare self-management support skills, using all scales of the SEPSS-36, before and after the experimental period (T0-prior to training and T1-at the end of the implementation period). For non-normally distributed data, we will use the Wilcoxon signed-rank test and the paired samples *t* test in case of normally distributed data.

The video recordings of the NPs will be assessed in blocks of 5 minutes each. Of every recording, a 5-minute clip will be randomly assigned to be observed by two researchers independently. The clips from the control period will be compared with the clips of the experimental period on the needs-thwarting and needs-supporting subscales and tested using the Wilcoxon-signed rank test for non-normally distributed data and the paired samples t-test in case of normally distributed data.

The interviews and qualitative questions in the questionnaire, which will be used to qualitatively evaluate the intervention and the nurse-led care, will be transcribed by at least two researchers independently and analysed thematically [55] using NVivo.

To examine if contamination occurred, we will compare the primary outcome (Skills and Technique Acquisition - heiQ) among control period patients in the contamination phase versus those in the control period not in the contamination phase at T1 and T2. This will be done using an independent samples *t* test. If there is a significant difference, we will control for contamination in the main multivariate analysis.

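### The correction for contamination depends on an unadjusted significance test that would usually miss contamination worth correcting

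*Protocol article*

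**What the plan says.** The protocol's Data analysis section compares, on the heiQ Skills and Technique Acquisition scale, "control period patients in the contamination phase versus those in the control period not in the contamination phase at T1 and T2". On the method it says "This will be done using an independent samples" t test; no covariate, baseline value, department or date enters. The consequence is fixed: "If there is a significant difference, we will control for contamination in the main multivariate analysis". The threshold is the general one in the same section, "value < 0.05 is considered statistically significant". The protocol does not say whether T1, T2 or either one decides.

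Other sections bear on the point:

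- **Study design and randomization** describes the risk in terms of the month in which the nurse practitioners (NPs) are trained. It sets two precautions: standard care for all control patients, and questionnaires sent by the researcher.
- **Strengths and limitations** describes the risk more widely, as any control patient treated and followed up after the NP was trained. These patients will be registered, and the group is expected to be small and without influence.
- **Sample size** counts contamination among the reasons for going from 82 to 100 patients per group.

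No section makes the correction unconditional.

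**The concern.** The rule lets a significance test decide whether the multivariate model allows for contamination. Such a test is useful only if it would probably detect contamination large enough to matter, and if it responds to contamination and little else. Neither is assured here. The test uses only the control half of a trial that was sized for a baseline-adjusted comparison of both halves. The contaminated controls also differ from the others by design in department, and each department treats a single organ.

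At stake is an effect diluted toward zero, together with a report that contamination was examined and not found.

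**Working it through.** **Inputs from the protocol.** Effect size: "we estimate the effect size of the intervention to be 0.38, which is the average effect size observed in the previous studies". Sample size: "82 patients per group are needed to obtain a power of 80% to detect a significant effect of the intervention". The test is two-sided with alpha 0.05. Planned recruitment is 100 per group. All seven departments start control recruitment in September 2020, and the first crosses over in March 2021. T1 is at 6 months and T2 at 12 months.

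**Assumptions, because the protocol gives no figure.** Contaminated share p of 10-50%. Contamination effect δ from 0.19 SD (half of 0.38) to 0.38 SD (all of it).

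**1. The plan's own figure.** n per group = 2(1.96 + 0.84)²(1 − ρ²)/0.38². With ρ = 0 this gives 109. With a baseline correlation ρ = 0.5 it gives 81.5, that is 82. The stated number is reproduced with ρ = 0.5, which the protocol does not state and which is used in step 4.

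**2. Power of the contamination test.** Two-sample t test, two-sided 0.05, SD 1, noncentrality δ/√(1/n₁ + 1/n₂). Example: 50 v 50 and δ = 0.38 gives 0.38/0.20 = 1.90 against a critical value of 1.98, so power is 47%.

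| Controls | Contaminated v other | δ = 0.19 | δ = 0.38 |
|---|---|---|---|
| 100 | 10 v 90 | 9% | 20% |
| 100 | 15 v 85 | 10% | 27% |
| 100 | 20 v 80 | 12% | 33% |
| 100 | 50 v 50 | 16% | 47% |
| 82 | 8 v 74 | 8% | 17% |
| 82 | 16 v 66 | 10% | 27% |
| 82 | 41 v 41 | 14% | 40% |

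For 80% power at an even split, the formula in step 1 with ρ = 0 requires 109 controls per subgroup (218 in all) at δ = 0.38, or 435 per subgroup (870 in all) at δ = 0.19.

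If significance at either T1 or T2 is enough, simulation with 100 controls, the same split at both visits and a T1-T2 correlation of 0.5 to 0.7 gives 14-64%. It passes 50% only with a large share and the full effect. Without any contamination, testing twice raises the false-positive rate from 5% to 8-9%.

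**3. Confounding and group size.** Controls in the first department enter from September 2020, so their T1 falls in March 2021 or later, at or after crossover. Under the wider definition that department supplies essentially no uncontaminated T1 controls. At T2 the same holds for any department that crosses over by September 2021.

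Now assume even accrual and seven evenly spaced crossovers, from month 6 to a last one between months 12 and 20. The mean control period is then 9 to 13 months.

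- T1 after crossover: 6/9 = 67% down to 6/13 = 46% of controls.
- T2 after crossover: 100% down to 80%.
- Only controls enrolled in the last month before crossover: 1/9 = 11% down to 1/13 = 8%.

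So the group is small under one reading and about half of controls under the other.

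False triggering without contamination was simulated for a single test with half of the controls flagged, crossovers over months 6 to 18 and intracluster correlation 0 to 0.10. The rate was about 5-7% with no time trend, 7-9% with 0.2 SD per year and 11-14% with 0.4 SD per year.

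**4. Cost of skipping a needed correction.** Observed effect = 0.38 − p × δ; power at 82 per group with ρ = 0.5.

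| p | δ | Observed effect | Power |
|---|---|---|---|
| none | none | 0.38 | 80% |
| 15% | 0.19 | 0.38 − 0.0285 = 0.35 | 73% |
| 20% | 0.19 | 0.38 − 0.038 = 0.342 | 71% |
| 50% | 0.19 | 0.38 − 0.095 = 0.285 | 55% |
| 50% | 0.38 | 0.38 − 0.19 = 0.19 | 29% |

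**The case against.** The strongest reply has four parts.

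- **The plan took care.** It has preventive steps, registration of affected patients and a larger sample. This stands, and it limits the damage. At 100 evaluable per group, power in the case of half the controls at half the effect is about 64% rather than 55%. None of these steps removes the conditional rule.
- **Dilution works against the intervention.** Uncorrected contamination would not create a false positive in a superiority trial. This also stands; the cost is a missed or understated effect.
- **The test is least sensitive where contamination matters least.** A reader might infer from the table that harmful contamination goes unnoticed up to 90% of the time. That does not follow. The 90% miss rate belongs to 15% contaminated at half the effect, where the dilution is about 0.03 SD. Where the dilution is 0.19 SD, the miss rate is 53%.
- **Calendar confounding is only partial.** Contaminated controls are late relative to their own department's crossover, not necessarily late in the trial. Those of the first department enrolled first of all, and late-switching departments supply uncontaminated controls at later dates. A reader might infer that a time trend would usually trigger the correction wrongly. The 5-14% above does not support that.

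Nor does the test choose the whole main analysis, as might be inferred. It governs one term in the multivariate model. The Data analysis section also gives the label of primary analysis to an uncorrected univariate comparison at T1, whereas Sample size attaches it to the mixed model.

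**Conclusion.** The point holds in a limited form. The plan conditions the correction on an unadjusted test whose power stays below 50% at a single time point in every scenario considered. Following the rule would usually leave contamination uncorrected, and a non-significant result says little. Confounding with department and organ follows from the protocol's own dates and structure; confounding with calendar time is partial, and false triggering is a secondary risk.

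The rule and its conditional wording are certain. The percentages are not properties of the protocol: they rest on the assumed shares, effects, accrual and baseline correlation. The consequence runs from slight (about 0.03 SD at 15% contaminated and half the effect) to substantial (0.095 SD and a fall in power from 80% to about 55% when half are contaminated at half the effect). Which end applies depends largely on which of the two descriptions of the contaminated group is meant.

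**What to change.** 1. Delete the rule that makes the correction depend on significance.
2. Keep the intention-to-treat mixed model as the main analysis, without a compulsory contamination term. If about half of the T1 controls and most T2 controls were flagged, forcing that term in could cost much precision at T1 and leave the T2 effect barely estimable.
3. Define contamination by visit, for example as a control-period measurement taken after the department's NPs were trained, and use that definition throughout.
4. Prespecify a sensitivity analysis at T1, reported whatever the p-value, that excludes post-training control measurements or flags them by visit, adjusted for department and calendar period. Report the contamination estimate with its confidence interval.
5. Report the T2 version only where it is estimable.

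The change needs analysis wording and some analysis work; contamination status is already being registered. The price is precision. Under the illustrative accrual, excluding flagged measurements would leave about 33 to 54 of 100 controls at T1 and 0 to 20 at T2. This is why it belongs beside the main analysis and not in its place.

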## Discussion

In the proposed multi-centre study, we will test the effect of the ZENN intervention (22) on organ transplant recipients, with a stepped-wedge clustered randomized controlled trial. It is also of interest to learn if the training to deliver the programme has an effect on NPs self-management support skills. This study was designed as a mixed-methods study, with a multidisciplinary research group.

### Strengths and limitations

Some strengths and weaknesses of the study design can be identified. The overall strength of the study is that we give patients in the experimental group the opportunity to participate in an intervention that may meet the needs of patients for holistic and tailored self-management support. Existing interventions have an insufficient tailoring to individual needs [18, 22, 56]; therefore, this intervention has the potential to make an important contribution to the lives of transplant recipients and approaches available to post-transplant professionals.

A strength of the stepped wedge design in this study is that the participating departments will be randomized so that, every department will have the opportunity to participate in the experimental period. With a classical randomization, whereby patients, NPs, or departments would be randomized into the control and the experimental arm, half of the patients would not receive the intervention or half of the NPs would not be trained. Randomization at the patient level is not possible due to the fact that nurses learn communication techniques and it is not possible to switch between these techniques during the control and experimental arm. Moreover, randomization at the NP level would be less preferable. Some departments have only one NP and if they will be randomized into the control arm, a whole department would not be able to participate in the intervention.

A limitation of the stepped wedge design is the risk of contamination of control period patients. Although the stepped wedge design eliminates to a great extent control-period patients being treated by a nurse trained in the intervention, there will be some patients at the end of the control period who are treated by and who undergo follow-up measurement once their NP has been trained. This means that it is possible that the patients at the end of the control period may be ‘contaminated’. We will register which control period patients fall into this ‘contamination phase’. We expect that this will be a small group and not be of influence on the findings.

A second potential limitation is that the effect on the patients is dependent on the effectiveness of the training in bringing change among the NPs. The fact that NP’s spend extra time with the patient could also increase patients’ self-management skills. To identify if an increase of patients’ self-management skills is affected by the intervention, we will conduct an evaluation of the intervention fidelity and ask patients to evaluate the programme.

Another potential limitation is response burden due to the amount of questionnaires patients’ need to complete. At each point in time, the patients are required to complete four questionnaires, which together comprise 117 questions and time to complete the questionnaires will be approximately 30 min. It has been suggested that shorter questionnaires can increase response rate and that respondents will be less likely to drop out and to complete the questionnaire if it takes 10 min compared to when it takes 30 min to complete [57]. Although there is a chance of response burden, we decided to accept this due to the fact that these questionnaires are the most appropriate to answer the research questions.

Another strength of the study is that we have broadened the target group to include other organ types, compared to the pilot study [22]. In the initial pilot study, the target group consisted of kidney transplant recipients, but we believe and research has shown, that self-management support is important for all transplant recipients regardless of the organ [13, 19, 20]. While the cause of organ failure differs, the post-transplant treatment regime, accompanying challenges and needs such as adjusting daily life, food hygiene and immunosuppression, but also psychosocial challenges are partly the same. Therefore, this study will include patients who received a heart, kidney liver or lung transplantation and still have a homogeneous study group. If found to be effective, we will have evidence to support implementation among all these transplant recipients.

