**Methods:**

This multi-centre stepped-wedge randomized controlled trial will take place from September 2020 until May 2023. All departments will commence with inclusion of patients in the control period. Each department will be randomly assigned to a start date (step in the wedge) to commence the experimental period. Patients in the control period will receive standard care and will be asked to complete questionnaires at baseline (T0), 6 months (T1) and 12 months (T2), to assess self-management, self-regulation, quality of life and adherence. During the experimental period, patients will receive standard care plus the ZENN intervention and receive the same set of questionnaires as participants in the control period. Nurse practitioners will complete a baseline and follow-up questionnaire to assess differences in self-management support skills. Video recordings of outpatient clinic consultations during the control and experimental periods will determine the differences in nurses’ needs-thwarting and needs-supporting skills between the control and experimental period.

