## Methods/design

### Study design and randomization

This multi-centre study in the Netherlands has an unblinded stepped wedge cluster randomized design [32] with pre- (T0) and post-intervention measures after six months (T1), with a follow up after twelve months (T2). The framework of this trial is superiority, whereby we will compare the outcomes between the control and intervention group, and between baseline and follow up data. Seven departments of five University Medical Centres will participate in the study, four kidney transplantation units, one heart transplantation unit, one liver transplantation unit and one lung transplantation unit. The coordinating centre is Erasmus MC, department Nephrology and Transplantation. This department is responsible for coordinating the study, distributing the questionnaires, training of the NPs and the data analysis. A steering committee is present to contribute ideas and to oversee the process.

Given the nature of the programme and the fact that NPs are trained in delivery of the intervention and communication skills, the NPs delivering the intervention cannot be blinded to the group allocation. Therefore, randomization will be performed at the department level. This will be carried out by an independent professional not involved in the study using sealed opaque envelopes. The envelopes with department names and envelopes with start date will be prepared and shuffled by the researcher. The independent professional then randomly chooses the envelopes. All seven participating departments commence the study with standard care i.e. the control period (see Fig. 1) in September 2020. The timing of transition of departments from control to experimental  period is randomized. The first department will be randomized to commence the experimental period in March 2021. During the experimental period, patients receive standard care plus the ZENN intervention. Patients in the control period are different from the experimental period patients, meaning that they will not cross-over.

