**Fig. 1 Fig1:**
[figure not shown]
Flowchart of the study

In the month prior to the initiation of the experimental period for each department, the NPs will be trained in the delivery of the intervention. At this point in time, there will still be patients in the control period who are yet to complete the follow-up measure. During this month they may receive care in the form of a standard consultation from this NP. Therefore, there is potential for ‘contamination’ of these control period patients in the sense that their NPs will have already received the training associated with the intervention. To limit the risk of contamination, the following strategies will be put in place: standard care protocol will be used in all consultations for control period patients, and the questionnaires will not be administered by the NP but will be sent out by the researcher.

The ZENN intervention will be conducted in the outpatient clinic of each participating department. Due to the COVID-19 pandemic, the possibility of carrying out the intervention through tele-medicine is being examined. For the schematic overview of the inclusion, see Fig. 1. To enhance the validity of the study, the Standard Protocol Items: Recommendations for Interventional Trials (SPIRIT) guidelines [33] will be followed.

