### Training

At the moment of transition to the experimental period, NPs will receive training in communication skills and intervention background by a psychologist ([name]). Both trainers were part of the team who developed the ZENN intervention. The content of the standardized training includes knowledge of the steps in the programme protocol, theoretical knowledge of behaviours change techniques, and practicing these techniques through role-play. NPs learn to activate patients to generate their own solutions rather than focusing on the problems and achieve progression towards personal goals in short space of time. The training consists of two blocks of three hours given on the same day. Due to the COVID-19 pandemic, the possibility of carrying out the training through e-learning and video conferencing is being examined. In addition, there is a booster session once implementation has begun with the aim of discussing cases and optimizing standardization between NPs. The experimental period starts immediately the day after the one-day training has been completed. An extensive description of the training according to the CRe-DEPTH criteria developed by Van Hecke et al. (2020) [38] can be found in Supplement A.

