## Trial status

Start of inclusion; September 2020, expected end of inclusion May 2022.

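### The expectation that contaminated controls are a small group does not fit the plan's own dates, and the window that defines them is described in three different ways

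*Protocol article*

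**What the plan says.** The calendar is given in three places of the protocol article.

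- Study design and randomization: "All seven participating departments commence the study with standard care i.e. the control period (see Fig. 1) in September 2020", and "The first department will be randomized to commence the experimental period in March 2021".
- Abstract, Methods: T1 is at 6 months and T2 at 12 months after baseline.
- Trial status: "Start of inclusion; September 2020, expected end of inclusion May 2022".

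The exposure of controls to trained NPs is also described in three places.

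- Study design and randomization, text after Fig. 1: "In the month prior to the initiation of the experimental period for each department, the NPs will be trained". For controls with follow-up outstanding it adds: "During this month they may receive care in the form of a standard consultation from this NP".
- Training: "The experimental period starts immediately the day after the one-day training has been completed".
- Strengths and limitations: the affected controls are those late in the control period who are both treated by and followed up after a trained NP. They will be registered as being in a contamination phase. The section then concludes: "We expect that this will be a small group and not be of influence on the findings".

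The plan does provide for contamination. The Sample size section raises 82 per group to 100, partly for this reason. The Data analysis section compares controls inside and outside the contamination phase at T1 and T2 with a t test, and adjusts the multivariate model if the difference is significant. Controls are to be seen under the standard care protocol.

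**The concern.** Controls do not cross over, but their follow-up runs 6 and 12 months past inclusion. Anyone included within 6 months before the department's switch has T1 after the NPs are trained, and anyone included within 12 months before it has T2 after training. With a first control period of about six months, that is not a tail of late patients.

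The safeguard is weaker than it looks. Strengths and limitations argues against patient-level randomization on the ground that nurses cannot move back and forth between communication techniques. Asking trained NPs to give controls standard care relies on exactly that. Any carry-over would shrink the difference between groups at T1, the time point of the sample size calculation, and more so at T2.

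The definition matters as well, because the contamination phase is the grouping variable of the planned check. A window of one month before the switch leaves out consultations after the switch, when the NP is trained and control follow-up may still run for up to 12 months.

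**Working it through.** **1. Inputs.** Month 0 = September 2020. First switch = March 2021, month 6 (month 7 if at the end of March). End of inclusion = May 2022, month 20 (month 21 if at the end of May). T1 = 6 months, T2 = 12 months. The plan gives no number for the contaminated group, so there is no stated share to reproduce.

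**2. Results that need no accrual assumption.** The earliest possible control, included on 1 September 2020, reaches T1 about 1 March 2021 and T2 about 1 September 2021 (month 12). All other controls reach them later. Hence:
- with a switch at the start of March 2021, essentially every first-department control has T1 at or after the switch, and every one has T2 after it;
- every department that switches by month 12 has all its control T2 measurements at or after the switch.

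**3. Results that assume even accrual up to the switch.** For a switch at month L and follow-up at f months, the share measured after training is min(1, f/L), with training placed at the switch.

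| Switch month L | T1 | T2 |
|---|---|---|
| 6 | 100% | 100% |
| 7 | 6/7 = 86% | 100% |
| 12 | 6/12 = 50% | 100% |
| 20 | 6/20 = 30% | 12/20 = 60% |
| 21 | 6/21 = 29% | 12/21 = 57% |

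Month 20 is the most favourable case, since such a department would have almost no time left to include experimental patients.

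**4. Sensitivity at L = 20.**
- Accrual falling linearly to zero: (6/20)² = 9% and (12/20)² = 36%.
- Accrual rising linearly from zero: 1 − (14/20)² = 51% and 1 − (8/20)² = 84%.
- Control inclusion stopped 3 months before the switch: 3/17 = 18% and 9/17 = 53%.
- Training one month before the switch, even accrual: 7/20 = 35% and 13/20 = 65%.

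**5. All departments together.** The later step dates are not in the text. With seven evenly spaced steps from month 6 to month 18–20 (assumed) and even accrual, about 46–57% of all controls have T1 and 80–90% have T2 after training. The range covers weighting departments equally or by length of control period.

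**6. Possible influence on power.** The plan's own figure first: a t test with d = 0.38, two-sided 0.05 and 80% power needs 108.7 per group before rounding. Multiplying by 1 − r² with r = 0.5 gives 108.7 × 0.75 = 81.5, so 82 as stated. The plan does not give r; 0.5 is the assumption that reproduces its number. If a share p of controls takes up a fraction c of the effect, the detectable difference is 0.38 × (1 − p·c). With p = 0.5 and the planned 100 per group:
- c = 0: d = 0.38, power 87%;
- c = 0.25: d = 0.3325, power 78%;
- c = 0.5: d = 0.285, power 64%.

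The 100 must also cover dropout, missing data and covariate adjustment, so these are upper values.

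**7. The planned check.** Suppose 100 controls split 50/50 and a carry-over of half the effect, 0.19 SD. The test statistic has mean 0.19 × √(50/2) = 0.95, and the chance of exceeding 1.96 is about 16%. A carry-over of that size would usually go unadjusted. Moreover, the first department has essentially no uncontaminated controls, so the test partly compares departments.

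**The case against.** The strongest reply is that the plan discloses the risk and acts on it: it enlarges the sample, keeps controls on standard care, registers affected patients and tests for a difference. This is true, and it would be wrong to say that contamination was ignored. But it does not make the group small, and the test has little power to trigger the adjustment.

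Several limits stand.

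- A measurement after training is not the same as treatment by a trained NP, which the plan's definition also requires. A control whose T1 falls just after training may have had no consultation in between. The shares above are upper limits on real exposure.
- Controls do not receive the Self-Management Web, goal setting or the session series, so carry-over may be slight. With none, power is unchanged.
- A reader might infer that at least 30% of T1 and 60% of T2 measurements are affected in every department. The documents do not support that as a minimum: it needs even accrual up to the switch, which is nowhere stated. Eligibility from 2 to 13 months after transplantation means that a pool of patients exists on the first day, so front-loaded accrual is plausible. Fig. 1, the inclusion schematic, is not shown.
- Training on the day before the switch does fall within the preceding month, so those two sections are not flatly contradictory. Together, however, they can reduce the month of exposure to a single day, while Strengths and limitations extends exposure to follow-up.
- Contamination in the direction of benefit dilutes the effect; it does not by itself create a false claim of superiority.

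**Conclusion.** The point holds as a mismatch between a stated property and the plan's dates. In the first department essentially all control T1 measurements (about 86% with a late-March switch and even accrual) and all T2 measurements come after NP training. For any department switching by month 12, all control T2 measurements do. Even the latest conceivable switch leaves about 30% and 60% under even accrual, with ranges of 9–51% and 36–84% under falling or rising accrual.

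What the dates contradict is the size of the group. The expectation of no influence is unsupported rather than disproved, because carry-over is unknown; the 87%, 78% and 64% are illustrations resting on r = 0.5, half the controls affected and assumed carry-over. A reader might also infer that the aim of showing sustained change is lost. That goes too far, since the Data analysis section also plans T0–T2 comparisons within each period. It is the between-group comparison at T2 that will be made largely against controls measured after training.

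**What to change.** 1. Replace the sentence on a small group without influence by the share of control T1 and T2 measurements expected after training, computed from the actual step dates.
2. Reconcile Study design and randomization, Training, and Strengths and limitations into one definition, set per measurement: a control-period T1 or T2 taken after the department's NPs were trained, ideally with a consultation in between.
3. Replace the adjustment that depends on a significant t test by a prespecified sensitivity analysis that adds a time-varying contamination indicator to the mixed model.
4. Add a T1 analysis that excludes control measurements after training, where enough remain. Do not extend this to T2, where it could remove most or all controls.
5. Describe the T2 between-group comparison as one against largely post-training controls.

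The cost is small: wording, one indicator and one or two extra analyses, using training and questionnaire dates that the trial should already hold; consultation dates are needed only for the stricter definition. The downside is some loss of precision, and the indicator is partly confounded with department and calendar time, so its coefficient should be read with caution.
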